#### Local Interim Data Analysis/Data Monitoring Plan

**Data Safety Monitoring Plan**

Our data and safety-monitoring plan will involve monitoring by the principal investigator, a safety officer from the Joslin Diabetes Center, [name], along with our Institutional Review Board (IRB). The possible adverse events (AEs) that warrant reporting include significant symptomatic hypotension during the ultra-sound test following the administration of sublingual nitrates. In the protocol involving vascular ultrasound, sublingual nitroglycerine 0.4mg is administered to subjects who will assume the recumbent position while having his/her blood pressure monitored. The blood pressure will continue to be monitored when patient assumes the sitting position after 15 minutes of recumbence. The subject will return to recumbent position until the effect of nitroglycerine wears off if the subjects cannot tolerate the sitting or standing position. The DEXA scanning is considered non-invasive. All adverse events will be clearly documented in specific reporting forms, and reported by the principal investigator to the IRB and the Clinical Research Center (CRC). Adverse events will also be reported to the NIH Office of Biotechnology Activities (OBA) if required. In the event of any medical instability, the nurse coordinator will contact [name], [contact], or [name] [contact].

**POSSIBLE BENEFITS:**

There may not be any immediate benefit from participating in the study. However, the findings of the study may provide future directions on the prevention and lifestyle/medical treatment for diabetes in both Asian and Caucasian populations.

**POSSIBLE RISKS:**

Because this study primarily involves changes from one typical diet to another, we expect a very low risk to benefit ratio.

In this study the risk and discomfort may include:

**Oral Glucose Tolerance Test (OGTT)**

Subjects will be asked to drink a beverage with 75 g of glucose. Slight nausea may be experienced due to the concentration of sugar in the test medium.

**Blood Loss/Blood draw**

The total amount of blood drawn during the study is about 2 fluid ounces. This amount should not pose any risk to subjects.

**DEXA Scan**

The risk associated with the body composition test includes some exposure to low-level radiation. Exposure to radiation from a whole body DEXA for body composition is not excessive. While no amount of radiation has been proved to be safe, there is no direct evidence that the small doses of radiation used in this study, similar to those used in diagnostic radiology, cause harmful effects in the person who is exposed. The total effect of radiation dose from the DEXA test is less than 5 percent of the effective natural background radiation a person receives from living in a typical American community for one year. It is about the same radiation as that received from three coast-to-coast airline flights.

Lying still on a firm surface for a total of 20 minutes may cause minor discomfort.

**Ultrasound**

The procedures in the vascular study involve stopping the blood flow in the subject's forearm with a blood pressure cuff for 5 minutes. This may cause some numbness or discomfort in the arm. This will disappear soon after the cuff is released. Occasionally, minimal bruising occurs in the area where the cuff was inflated. This will disappear in a few days.

Subjects will be given Nitroglycerin during the blood vessel ultrasound exam, which can cause slight headache or dizziness. These reactions are usually temporary and do not require any formal treatment. For people taking Viagra, Cialis or Levitra the use of these medications may cause a harmful interaction with the nitroglycerin used in the ultrasound study, there we advise subjects not to take Viagra for 24 hours and Cialis and Levitra for 72 hours before participating in the ultrasound test. On the day of the test, we will ask the subject if he or she is taking Viagra.

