**Details of Study Procedure(s)**

**Visit 1 – Screening (Week 0 – Week 2)**

Prior to Visit #1, all subjects will be screened by a checklist (base on inclusion/exclusion criteria listed in Part C). Each will be asked to fast before coming to the visit.

Eligible subjects will be scheduled for **Visit 1 (beginning of week 0)** with a study physician who will collect the consent forms from Joslin Diabetes Center and Beth Israel Deaconess Medical Center. Medical history, physical examination, anthropometric measurements, blood tests, blood pressure, pregnancy tests for females, and an oral glucose tolerance test will be performed after this. Those who have blood glucose results > 200mg/dl from oral glucose tolerance test will be excluded from the study. A registered dietician will perform a 24-hour diet recall, counsel the dietary procedures and use of accelerometer. Total Energy Expenditure (TEE) for each subject will be calculated to determine caloric intake using the following equation:

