**Exclusion criteria:**

1. Acute weight loss/weight gain over the past 6 months (defined as +4 lbs or more/month)
2. History of diabetes
3. Current Smokers (including those who quit < 1 year)
4. Heavy alcohol drinkers, defined as drinking more than 7 drinks/week. Those who drink alcohol will need to be reported and documented. They will be asked to maintain the levels of alcohol consumption throughout the study.
5. Medical history of vascular diseases (CAD, MI, stroke, CABG, angioplasty), diabetes, liver disease, kidney disease, cancer, AIDS, bleeding disorders
6. History of food allergies or to any food products in the diet menu
7. Enrolled in another investigational study within 1 month prior to screening for this study
8. Vegetarian, those with significant food aversions, and anyone who cannot comply with the diet
9. Pregnancy or breasting feeding
10. Other autoimmune or inflammatory conditions or diseases that may compromise the patient's safety or compliance during the study on an individual basis
11. Chronic use of antibiotics or anti-inflammatory medications (>1 month) within the past year
12. On medications such as statins, angiotensin converting enzyme inhibitor, warfarin, aspirin or other anti-inflammatory medications. Daily multivitamins are permitted, excluding pharmacological doses of anti-oxidants will not be allowed.
13. *Individuals with dental needs requiring extensive dental restorations such as cavities, root canals, crowns, etc.*

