**Unforeseen Risks**

There may be other risks not yet identified

Adequacy of Protection Against Risks:

Procedures to protect against potential risk:

**OGTT**- The test medium will be pre-chilled to minimize nausea

In the protocol involving vascular ultrasound, sublingual nitroglycerine 0.4mg is administered to subjects who will assume the recumbent position while having his/her blood pressure monitored. The blood pressure will continue to be monitored when patient assumes the sitting position after 15 minutes of recumbence. The subject will return to recumbent position until the effect of nitroglycerine wears off if the subjects cannot tolerate the sitting or standing position. The possible adverse events (AEs) that warrant reporting include significant symptomatic hypotension during the ultra-sound test following the administration of sublingual nitrates.

The DEXA scanning is considered non-invasive. All adverse events will be clearly documented in specific reporting forms, and reported by the principal investigator to the IRB and the Clinical Research Center (CRC). Adverse events will also be reported to the NIH Office of Biotechnology Activities (OBA) if required. In the event of any medical instability, the nurse coordinator will contact [name], [contact], or [name] [contact].

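### The test-day question before nitroglycerin covers one of the three drugs the protocol names as a harmful interaction

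*Protocol*

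**What the plan says.** The Ultrasound paragraph under Possible Risks makes three statements in sequence.

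- The hazard: "For people taking Viagra, Cialis or Levitra the use of these medications may cause a harmful interaction with the nitroglycerin" used in the study.
- The advice: "we advise subjects not to take Viagra for 24 hours and Cialis and Levitra for 72 hours before participating in the ultrasound test".
- The check: "On the day of the test, we will ask the subject if he or she is taking Viagra".

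The dose and the precautions around it appear under Unforeseen Risks and again in the Data Safety Monitoring Plan: "sublingual nitroglycerine 0.4mg is administered to subjects who will assume the recumbent position while having his/her blood pressure monitored". Monitoring continues when the subject sits up after 15 minutes, and the subject lies down again if sitting or standing is not tolerated.

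The adverse event that both of those sections single out for reporting is "significant symptomatic hypotension during the ultra-sound test following the administration of sublingual nitrates".

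The Study Procedures Flow Sheet schedules the forearm ultrasound at Visits 2, 3 and 4.

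**The concern.** The hazard statement and the advice each cover three drugs, but the check covers one. If staff follow the text as written, users of Cialis or Levitra pass the test-day check without being asked about what they took.

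The nitroglycerin serves a research measurement in volunteers who, according to Possible Benefits, may gain nothing immediate from taking part. What is at stake is an avoidable reaction in a subject whom the protocol has already identified as at risk. The protocol calls the interaction harmful without naming its form. Symptomatic hypotension after nitrates is the event its safety plan watches for, so it is natural to expect the pre-dose question to guard against it. That link is a reasonable inference and is not stated in the text.

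**Working it through.** No power, alpha or sample-size figure is involved. The check is a comparison of the protocol's own statements.

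**1. Coverage within the Ultrasound paragraph**

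| Drug | Named as harmful with nitroglycerin | Advised abstention | Asked about on the day |
| --- | --- | --- | --- |
| Viagra | Yes | 24 h | Yes |
| Cialis | Yes | 72 h | No |
| Levitra | Yes | 72 h | No |

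The question covers 1 of 3 drugs. The two it leaves out have the longer window, by 72 − 24 = 48 hours. A Cialis or Levitra dose taken 48 hours before the scan breaches the advice, yet the subject can correctly answer no.

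The question is also in the present tense and carries no time window. The protocol does not say what follows a yes.

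**2. Could another step catch the same subject before dosing?**

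- *Exclusion criteria.* The medication item reads "On medications such as statins, angiotensin converting enzyme inhibitor, warfarin, aspirin or other anti-inflammatory medications". The list is open-ended, but none of the three drugs is named. The protocol manages them by advice to abstain and does not exclude users.
- *Visit 1 screening.* The content is "Medical history, physical examination, anthropometric measurements, blood tests, blood pressure, pregnancy tests for females, and an oral glucose tolerance test will be performed". A general history may reveal a regular user. It is taken before the ultrasound visits and cannot show what was taken in the 24 or 72 hours before Visits 2, 3 or 4.
- *Rights and Privacy.* Medications are among the items recorded from medical records. This too does not establish recent use on the test day.
- *Visit descriptions and Flow Sheet.* The ultrasound is listed at Visits 2, 3 and 4 with no drug check attached.
- *Data Safety Monitoring Plan and Unforeseen Risks.* Recumbency and blood pressure monitoring accompany and follow the dose. They limit the consequences of a fall in pressure and do not prevent a contraindicated dose.

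None of these is a test-day check for Cialis or Levitra.

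**3. How often the gap recurs**

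The Flow Sheet entries do not mention nitroglycerin, but the Ultrasound paragraph says it is given during this examination. Reading the two together gives three occasions per subject. For the 50 subjects in the first sentence of Study Design, that is 3 × 50 = 150 scans. For the 35 per ethnic group given later in the same section, it is 3 × 70 = 210. These are numbers of scans, not of drug users, which the protocol does not give.

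**The case against.** The strongest reply is that the question is only a back-up. All three drugs already carry advice to abstain, a regular user might be noticed in the screening history, the medication record or the screening forms (whose appendix is not shown), and the dose is given lying down with blood pressure monitored. Subjects are 25 to 55 years old with no history of vascular disease, so few may use these drugs. The single drug name could also be shorthand for the group just listed, which would make this a drafting slip in a risk description.

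Part of this stands. It would be too strong to say that no user could ever be identified: the gap is in the test-day check as written. The precautions around dosing are real and reduce the likely harm. The exclusion criteria need not name the drugs if advice and a question are the chosen safeguard.

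The rest does not remove the problem. The protocol added a question on top of its advice for one drug, and the reason for doing so applies equally to the other two. The shorthand reading is possible, but the sentence just before separates the drugs by name and by window, and staff or subjects taking the question literally will deal with Viagra only. Information gathered at or before Visit 1 cannot confirm abstention at later visits, whatever the unseen forms contain.

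**Conclusion.** The concern holds. The test-day check omits two of the three drugs that the protocol itself calls potentially harmful with nitroglycerin, at each of three ultrasound visits, and no other described step fills that place.

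The conclusion rests on reading the question as worded and on nitroglycerin being part of each scheduled ultrasound. The number of subjects exposed to the risk cannot be estimated from the protocol and may be small. The point has no bearing on the endpoint, the sample size or the analysis. It should be corrected because a hazard already recognised in the text is left partly unchecked and closing the gap is easy.

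**What to change.** Replace the single-drug question with one that matches the paragraph's own list. Before nitroglycerin at Visits 2, 3 and 4, ask whether the subject has taken Viagra in the past 24 hours, or Cialis or Levitra in the past 72 hours, and record the answer and the time of last use. The study physician should confirm the drug list and windows and specify the action after a yes, such as withholding nitroglycerin or rescheduling the scan. Add the item to the Flow Sheet entry for each ultrasound visit so that it is part of the procedure and not only of the risk text.

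The cost is one checklist line per ultrasound visit and an occasional rescheduled scan.

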**Asian Diets (AD) and Western/ American Diets (WD)**

Participants may expect a higher lipid profiles and blood glucose levels on either diet.

**Unforeseen Risks**

There may be other risks not yet identified

Adequacy of Protection Against Risks:

Procedures to protect against potential risk:

**OGTT**- The test medium will be pre-chilled to minimize nausea

In the protocol involving vascular ultrasound, sublingual nitroglycerine 0.4mg is administered to subjects who will assume the recumbent position while having his/her blood pressure monitored. The blood pressure will continue to be monitored when patient assumes the sitting position after 15 minutes of recumbence. The subject will return to recumbent position until the effect of nitroglycerine wears off if the subjects cannot tolerate the sitting or standing position. The possible adverse events (AEs) that warrant reporting include significant symptomatic hypotension during the ultra-sound test following the administration of sublingual nitrates.

The DEXA scanning is considered non-invasive. All adverse events will be clearly documented in specific reporting forms, and reported by the principal investigator to the IRB and the Clinical Research Center (CRC). Adverse events will also be reported to the NIH Office of Biotechnology Activities (OBA) if required. In the event of any medical instability, the nurse coordinator will contact [name], [contact], or [name] [contact].

**RECRUITMENT AND CONSENT PROCEDURES:**

A thorough search of the patient database (IDX and NextGen) at the Joslin Clinic and the Asian Clinic at Joslin will be undertaken to identify subjects with history of diabetes who have not, according to Joslin records, voluntarily opted out to be contacted for potential research studies. Since we are not studying diabetic individuals but healthy individuals with family history of diabetes, we will contact these individuals to ask their family members who may be interested to contact us for screening. In addition, we will enlist eligible Far East Asian Americans from: local Asian community health centers, from various college campuses and Asian American organizations. This will be done through advertisements placed on bulletin boards at medical centers, schools, or through referrals from colleagues. Subjects will also be recruited from fliers, advertisements, or through posting on the Internet. Invitation letters will be sent to eligible subjects. Advertisement samples will be presented for IRB approval prior to use. Subjects will receive informed consent form via mail prior to the initial visit. During the initial contact, a study investigator will explain the purpose, nature, and potential risks of the study in detail to the potential volunteer in languages they can understand. We plan to only include subjects who can understand English. If other Asian languages are needed to facilitate communication with subjects, they will be developed by professional translators and submitted for IRB approval. Brief questions will be asked to confirm demographic and medical information for eligibility. They will be given time to ask questions and make appointment for screening. Both genders are elicited equally to participate in the study.

***RIGHTS AND PRIVACY:***

**Please answer the following questions:**

- Will medical history/clinical information be obtained from the subjects’ medical records for the purpose of this study? If yes, please list what information will be recorded.

**X YES.**

List of information recorded:

- Anthropometrics
- Contact information
- Medical history
- Medications
- Lab results
- Will information resulting from this study (i.e. results of clinical/research lab tests, etc…) become part of the subjects’ medical record or provided to the subject and/or others for clinical purposes? If, no, please list what information will not be given to the subject or recorded in their medical record and why.

**X NO**, Ultrasound, Dexa, and specialized lab results will not be filed at subjects medical records because they may not have clinical relevance.

- Will subjects’ identifiable health information***** be shared with others outside of Joslin Diabetes Center? If yes, list whom this information will be shared with (please be specific, include names of collaborators, study sponsor contacts)?

**X YES**

Yes, the list will be shared with co-investigators from Harvard School of Dental Medicine since the dental intervention will be performed there.

***OMIT PROCEDURES / LEAVE STUDY:***

This is a voluntary study. Subjects have the right to omit specific procedures or to leave the study at any time during the study period. In cases of withdrawal or omitting certain procedures from the study, subjects are required to inform or/and provide a written and dated notice of the decision to the principal investigator or designated staff of the study.

***INCENTIVES / REMUNERATION:***

Subjects will receive a total $500 for participating in this study. They will first receive $50 after completion of visit 2; $ 150 after completion of visit 3 and $300 and a Bilingual Diabetes Guide (Chinese/English) after completion of Visit 4 (end of week 18). In addition, a total of 4 months of food will be provided to all subjects for the duration of the study. Free parking available upon each visit at Joslin (A total of 4 study visits and 6 short visits for weight measurement).

*** Identifiable Health Information**

Data that includes any of the following identifiers are considered identifiable health information:

- Name
- Social Security number
- Medical Record Number
- Address by Street Location
- Address by Town/City/Zip Code
- Date of Birth
- Admission or Discharge Date
- Date of Death
- Telephone Number
- Fax Number
- Electronic E-Mail Address
- Web URLs
- Internet Protocol (IP) Address
- Health Plan Beneficiary Number
- Account Number
- Certificate/License Number
- Vehicle Identification Number and Serial Number, including License Plate Number
- Medical Device Identifiers and Serial Numbers
- Biometric Identifiers (finger and voice prints)
- Full Face Photographic Image
- Any Other Identifier likely to identify the subject

***Please answer the following questions:***

1. Where and how will your project utilize the Joslin Diabetes Center?

**X CTU**

1. Will your project involve research on living human fetuses?

**No**

1. Does your project involve the use of any new drug or device?

**No**

1. Is review required by risk management foundation?

**No**

______________________________________________________ ____________________

